## Abstract

**Background::**

Archery has existed in human history for millenniums. Being a unique exercise and precision sport, the keys to performance are emotional control, attention, and concentration rather than explosive force, muscle power, and endurance. During the execution of archery, attention is the key to performance in elite players, especially in the initial period while drawing the bow. Auricular acupoint stimulation is one of the therapeutic methods of traditional Chinese medicine and has been reported for its use in amplifying the anesthesia effect, weight reduction, cessation of substance abuse, and autonomic nervous modulation.

**Methods::**

The study will recruit archery players in school teams among junior and senior high schools and colleges. The subjects will be randomly assigned to the ear and sham acupressure groups. This is a randomized controlled trial with crossover design. The outcome measures will be obtained, including the meridian activities and balance index with Ryodoraku device, the movement stability with WIMU tracking system, the continuous heart rate record, and the scores of the 2 sections as the performance. The subjects will rate their attention and fatigue levels through self-reported questionnaires.

**Objectives::**

This study aims to investigate the immediate effect of non-invasive auricular acupoint stimulation on the performance and meridian activities of archery athletes.

**Trial registration::**

ClinicalTrials.gov Identifier: NCT04637607.

## Introduction

1

Archery is a sport of using a bow to shoot arrows to a designated target with set distance and direction. It was first recorded as a sport in the ancient Egyptian and Chinese histories and is one of the oldest sports that is still practiced. Archery first appeared in the Olympic games in 1900, and has become a regular competition since 1972. Modern competitive archery games include target, field, Clout, crossbow, and flight archeries, etc. Modern popular bow types include compound, recurve, and barebow. Because of different setting and shooting methods, competitions of different bow types are held separately. Since there was no definite influence on performance in different weight classes, archers are divided into groups by different bow types and age according to the rules established by the World Archery Federation (formerly known as FITA from the Fédération Internationale de Tir à l’Arc).

Most sports performances are affected by power, muscular strength, and endurance. However, concentration, emotional control, attention, and stability are more important in precision sports such as archery, shooting, and golf.^[1,2]^ Archers must be stable, focused, and relaxed while performing without interference and fluctuating emotions. Some researchers pointed out that the mental status just before performing sports is the key to performance in precision sports.^[3,4]^ However, concentration and attention are easily disturbed during tournaments.^[5]^ The ability to concentrate from few seconds before action till launching is especially important to archers pursuing excellence.

The correlation between attention and heart rate variability (HRV) was first illustrated by the intake-reject hypothesis proposed by John I. Lacey. The hypothesis mentioned that the acceptance of external environmental stimulation or information is related to decreased heart rate, whereas its rejection is related to increased heart rate. There are multiple researches about precision sports and decreased heart rate. Hatfield et al^[3]^ found that during the aiming period of elite rifle marksmen, decreased heart rate was detected prior to trigger pull compared with baseline. Landers et al^[6]^ monitored heart rate activity of 11 right-handed adult archers during a 15-week beginning archery class. After 14 weeks of training, the archers showed improved performance accompanied with significant heart rate deceleration in the few seconds prior to arrow release compared with their pretrained conditions. Carrillo et al^[7]^ compared archery performance and autonomic nervous system (ANS) modulation by changes in HRV between 7 novices and 10 experienced adolescent archers. Compared with novices, experienced archers revealed a higher square root of the mean of squared differences between successive R-R intervals and a higher percentage of successive normal-to-normal intervals >50 ms. In other words, experienced adolescent archers presented a higher HRV, which may demonstrate a better regulation of parasympathetic nervous system. The activity of ANS plays an important role in archery. The activation of sympathetic nervous system not only increases heart rate, but diminishes stability and performance. Therefore, to activate parasympathetic nervous system well is essential to archers seeking optimal performance.

Auricular acupoint stimulation is one of the therapeutic methods in traditional Chinese medicine and is widely applied in treating various diseases. Previous literatures had concluded the use of auricular acupoint stimulation in amplifying the anesthesia effect,^[8]^ weight reduction,^[9]^ and the cessation of substance abuse.^[10]^ Auricular acupoints could be stimulated with invasive metal auricular needles or non-invasive stimuli, including magnetic beads and Vaccaria seeds.

Hsu et al^[11]^ conducted a research to evaluate HRV, pulse rate variability, and electroencephalogram in 10 healthy adults with electroencephalogram, electrocardiogram, and blood-pressure-pulse recorder after 10 minutes of acupuncture over Sishencong scalp acupoint and Shen-men auricular acupoint separately. Decreased heart rate, pulse rate, and blood pressure were shown after stimulation on either scalp or auricular acupoints compared with control. In frequency domain analysis after fast Fourier transform, the high and low frequency powers of HRV were respectively increased and decreased, which indicated that parasympathetic nervous system was activated and sympathetic nervous system was inhibited. Conclusively, acupuncture over either Sishencong scalp acupoint or Shen-men auricular acupoint might lower the heart rate and activate the parasympathetic nerves, and that is the exact principle to advance archery performance as mentioned above. By applying such effect, we could alleviate the negative effect caused by pressure during competition and improve concentration and stabilization, the necessary characters for archery. However, no previous literature has investigated the effect of acupuncture or acupressure on the autonomic nervous condition or meridian characteristics of archery athletes or their performance.

Combining the modern electrophysiology of nervous system and the meridian theory in traditional Chinese medicine, this randomized controlled study aims to investigate the immediate effect of non-invasive and sham auricular acupoint stimulation on the meridian activities through measuring Ryodoraku and observing whether auricular acupoints could regulate ANS condition, meridian activities, and thus affect performance in archery athletes.

## Methods

2

### Ethics approval

2.1

The study was approved by the human ethics committee of Chang Gung Medical Foundation institutional review board (IRB No. 201900969B0C501). The protocol has been registered at ClinicalTrials.gov (identifier: NCT04637607, latest version on January 6, 2021). All participants will provide their written informed consent. Personal information about participants will be collected, shared, and maintained in an independent closet to protect confidentiality before, during, and after the trial. Therefore, the participants will be presented as serial numbers and the conversion list will be stored appropriately in a locked closet. The principal investigator will have access to the final trial dataset.

### Study design

2.2

The study was started in October 2019 and planned to complete by December 2020. This is a crossover randomized controlled trial (Fig. 1). Each participant will be tested with 2 different interventions respectively. The participants will be randomized into ear-acupressure (EA) group (n = 17, anticipated) or sham-acupressure (SA) group (n = 17, anticipated), according to their order of appearance on the measuring day. Participants appearing in the odds order (1st, 3rd, 5th, etc) will be allocated to EA group whereas those appearing in the even order (2nd, 4th, 6th, etc) will be allocated to SA group. The trial participants and outcome assessors will be blinded after assignment to interventions using labels 1 and 2 for the 2 groups. The 2 interventions will be administered on the same day during 2 consecutive rounds of archery contest. The measurement will be performed at the archery ranges where participants used to practice archery.

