### Intervention

2.5

Ear acupressure: Vaccaria seeds are the mature seeds of *Vaccaria segetalis (Neck.) Garcke*, also known as cowherb, and wang-bu-lui-xing in Chinese. It is usually spherical in shape and about 1.5 to 2 mm in size. Vaccaria seeds will be attached by 3 M tape over auricular heart, liver, shen-men, and kidney points, under the application of the Chinese medicine physician who has >7 years of clinical service. Five minutes after administration, participants will start shooting a round of play with 36 arrows (within 40 minutes, including removal of arrows).

Sham acupressure: Same size of 3 M tape as in ear acupressure with a marked black point that looks similar to Vaccaria seed, will be attached over auricular heart, liver, shen-men, and kidney points. Five minutes after administration, participants will start shooting a round of play with 36 arrows (within 40 minutes, including removal of arrows).

Immediately after first round of play, the self-reported questionnaire will be filled out by the participants (V2). After sitting quietly for 15 minutes, the participants will receive Ryodoraku measurement. The Vacciria seeds/sham 3 M tape will be removed and switched to the other intervention (crossover) after the assessments are completed. Archers should rest for 15 minutes (including the time of obtaining written questionnaire and Ryodoraku measurement) between 2 rounds of play according to World Archery Federation rules. Next, the participants will start shooting the second round of play. Immediately after second round of play, the self-reported questionnaire will be filled out by the participants (V3). After sitting quietly for 15 minutes, the Ryodoraku measurement will be performed. Participants could cease the experiment if unbearable discomfort is experienced or unstable vital condition is observed during intervention, or under any personal request to stop the process.

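### The trial is called randomised, but treatment order is set by odd or even arrival, which is unconcealed alternation

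*Protocol article*

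**What the plan says.** The abstract of the protocol article states that "The subjects will be randomly assigned to the ear and sham acupressure groups". Section 2.2 (Study design) repeats the randomised label and then gives the mechanism. Allocation is made "according to their order of appearance on the measuring day", and the rule is that "Participants appearing in the odds order (1st, 3rd, 5th, etc) will be allocated to EA group whereas those appearing in the even order" go to the other group; the sentence ends "2nd, 4th, 6th, etc) will be allocated to SA group". No random list, random starting point, block or concealment step appears beside it.

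The same section says that "Each participant will be tested with 2 different interventions respectively", and section 2.5 (Intervention) has participants switch between the two rounds. Membership of the EA or SA group therefore means EA first or SA first.

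On blinding, section 2.2 says: "The trial participants and outcome assessors will be blinded after assignment to interventions using labels 1 and 2 for the 2 groups". The seeds are attached "under the application of the Chinese medicine physician who has >7 years of clinical service", and that physician is not among the roles listed as blinded. The Discussion adds that a preliminary test found the seed and the black mark alike in appearance.

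**The concern.** Random assignment of order is meant to do two things in a crossover. It makes the two sequence groups comparable except by chance, and it keeps everyone from knowing or steering the next assignment. Alternation by arrival secures neither by design.

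The setting makes this more than a formality. Participants come from school teams and are measured at their own ranges, so who arrives first may be visible to teammates, coaches and staff. Two of the four primary outcomes, the Checklist Individual Strength and the visual display terminal fatigue scale, are self-reported and therefore the most exposed if a participant learns the order. Both rounds are shot on one day with a short break between them, so fatigue building up over the session and a lingering effect of the first intervention are both plausible.

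**Working it through.** **1. The plan's own figure.** Section 2.4 gives 26 evaluable and 34 recruited participants, from an effect size of 0.48, α = 0.05, power 0.80 and 20% dropout. Take 0.48 as Cohen's f for a two-group between-factor comparison. Assume m = 3 measurements and correlation ρ = 0.5; the article states neither for this calculation. Then λ = f²·N·m/(1+(m−1)ρ) = 0.2304 × 26 × 3 / 2 = 8.99, which gives power 0.82, and 26 is the smallest even N that reaches 0.80. For dropout, 26/0.80 = 32.5, so 33, or 34 for equal groups. The allocation rule does not enter this calculation, so the fix leaves it unchanged.

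**2. Is there any random element?** Position in the arrival order goes in, its parity is taken, and the group comes out. For a given arrival order there is exactly one possible assignment. A random list restricted to 17:17 would have C(34,17) = 2,333,606,220.

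**3. How much can be foreseen?** The measure is the expected share of the 34 assignments guessed correctly by someone who knows the scheme:

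| Scheme | Correct guesses | Share |
|---|---|---|
| Odd/even arrival (as stated) | 34 of 34 | 100% |
| Simple randomisation | 17 of 34 | 50% |
| Random list restricted to 17:17 | 20.2 of 34 | about 59% |
| Permuted blocks of 4 | 2.83 of 4 | about 71% |

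For a block of 4, the chances of a correct guess are 1/2, 2/3, 2/3 and 1. They sum to 2.83, and 2.83/4 = 0.71. The 59% and 71% figures also require the guesser to know every past assignment. The odd/even rule needs only the rule and the arrival position, and it is fully predictable from the first participant.

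**4. Where can bias enter a crossover?** Let τ be the EA-minus-SA effect. Let π be the shift from round 1 to round 2, with value π₁ in those who have EA first and π₂ in those who have SA first. Let λ_E and λ_S be the carry-over of each intervention into round 2. The EA-minus-SA difference within a person is on average:

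- EA first: τ − π₁ − λ_E
- SA first: τ + π₂ + λ_S

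The equally weighted average is τ + (π₂ − π₁)/2 − (λ_E − λ_S)/2. Stable differences between persons cancel. What remains is a difference in period shift between the sequence groups, and unequal carry-over. The carry-over term would be present under true randomisation too. What alternation removes is the assurance that the groups differ in these respects only by chance. The article gives no value for any of these terms.

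**5. Blinding.** Parity of arrival determines the sequence, and in a two-period crossover knowing one round's intervention reveals the other's. The labels hide the sequence only from people who lack either the rule or the arrival order.

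**The case against.** The strongest reply is that the crossover takes most of the force out of this. The rule never decides who receives ear acupressure, only when, and within-person comparison removes stable differences between archers. That stands, and it limits the harm to the routes in step 4 and to unblinding.

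Second, a reader might infer that arrival order confounds the comparison because it relates to school, age, keenness or time of day. The document does not support this. Such traits matter only if they track odd versus even position, or if places are swapped. Alternation puts neighbours in opposite sequences, so a team arriving together or a steady trend over the day is split almost evenly. The article describes no swapping and gives no motive for preferring one order.

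Third, a reader might infer that blinding is broken. That goes too far. It would require knowing both the rule and the arrival order, and the article does not say that participants, coaches or assessors are told the rule. The preliminary test of similar appearance also counts in the plan's favour, although it bears on whether the tapes can be told apart and not on whether the next assignment is hidden.

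Fourth, a reader might tie the harm to a comparison of first rounds or to a period-adjusted model, or might expect unequal groups if the count restarts each day. Section 2.7 names neither analysis, only repeated-measures analysis of variance. The number and size of measuring days are not given, so no imbalance can be calculated.

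None of this removes the contradiction between the label and the stated method. Nor is it a detail left to a fuller document, because the article states the rule completely.

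**Conclusion.** The point holds in a limited form. The article describes as randomised an allocation that is deterministic and unconcealed. All 34 assignments can be foreseen, and could be altered, by anyone who knows the rule and sees the order of arrival; the fair comparison is about 71% for permuted blocks of 4, not only the 50% of simple randomisation. For such a person the labels may not preserve blinding, chiefly a risk for the two questionnaire outcomes.

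The effect on the result cannot be sized. It is confined to the order of the interventions and would act through period, carry-over or unblinding effects. That bias or unblinding will in fact occur is not shown. The correction is needed whatever its size, because the stated method contradicts the design label.

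**What to change.** Section 2.2 gives October 2019 to December 2020 as the study period, and section 2.1 cites a registry version of January 6, 2021, so allocation may be complete even though the article is written in the future tense. Both actions below are therefore main actions.

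- **Participants already allocated:** describe the trial as quasi-randomised by alternation in the abstract, the methods and the report, and state the lack of allocation concealment as a limitation.
- **Anyone not yet allocated:** replace the odd/even sentence with wording such as: *The sequence (EA then SA, or SA then EA) is taken from a computer-generated 1:1 list in permuted blocks of randomly varying size. The list is prepared by someone who takes no part in recruitment or assessment, and is held in sequentially numbered, opaque, sealed envelopes, each opened only after that participant's baseline measurements.*

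The cost is one list with its envelopes and a less favourable design label. No participants or measurements are added, and the 26 evaluable and 34 recruited stay as planned.

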**Figure 1 F1:**
[figure not shown]
Flow diagram of the experimental design. VDT = visual display terminal.

### Participants

2.3

Volunteered participants will be recruited from school teams among junior and senior high schools, and colleges in Kaohsiung, Taiwan through poster announcements in schools with archery club or school team and through internet. The investigator anticipates to enroll 34 participants, 17 each on EA and SA groups. Basic information including training duration of archery (1–3, 3–5, 6–10, and >10 years) and medical history will be collected. Inclusion criteria are healthy archers between 13 and 26 years old, who had been training for >1 year. Exclusion criteria include history of psychiatric disorders or cardiovascular diseases and previous surgical history of dominant hand. Those who are unwilling to provide informed consent will also be excluded. The study procedures and possible risks will be well explained to all the participants.

### Sample size

2.4

26 participants were estimated to be needed based on repeated-measures analysis of variance with an effect size of 0.48, a significance level (α) of 0.05, and a desired power (1–β) of 0.80. The effect size was calculated from previous literature with G∗power, version 3.1.9.7 (Faul et al, 2020).^[12]^ In the study conducted by Molassiotis et al,^[13]^ the mean (standard deviation) of general fatigue scores at the baseline before the treatment were 16.6 (2.7) at the acupressure group, and 17.8 (2.5) at the sham acupressure group, and the mean (standard deviation) of general fatigue scores after completing the treatment were 14 (2.4) at the acupressure group, and 16.9 (3.0) at the sham acupressure group. Taking the potential 20% drop-outs into account, a total of 34 participants will be recruited.

### Intervention

2.5

Ear acupressure: Vaccaria seeds are the mature seeds of *Vaccaria segetalis (Neck.) Garcke*, also known as cowherb, and wang-bu-lui-xing in Chinese. It is usually spherical in shape and about 1.5 to 2 mm in size. Vaccaria seeds will be attached by 3 M tape over auricular heart, liver, shen-men, and kidney points, under the application of the Chinese medicine physician who has >7 years of clinical service. Five minutes after administration, participants will start shooting a round of play with 36 arrows (within 40 minutes, including removal of arrows).

Sham acupressure: Same size of 3 M tape as in ear acupressure with a marked black point that looks similar to Vaccaria seed, will be attached over auricular heart, liver, shen-men, and kidney points. Five minutes after administration, participants will start shooting a round of play with 36 arrows (within 40 minutes, including removal of arrows).

Immediately after first round of play, the self-reported questionnaire will be filled out by the participants (V2). After sitting quietly for 15 minutes, the participants will receive Ryodoraku measurement. The Vacciria seeds/sham 3 M tape will be removed and switched to the other intervention (crossover) after the assessments are completed. Archers should rest for 15 minutes (including the time of obtaining written questionnaire and Ryodoraku measurement) between 2 rounds of play according to World Archery Federation rules. Next, the participants will start shooting the second round of play. Immediately after second round of play, the self-reported questionnaire will be filled out by the participants (V3). After sitting quietly for 15 minutes, the Ryodoraku measurement will be performed. Participants could cease the experiment if unbearable discomfort is experienced or unstable vital condition is observed during intervention, or under any personal request to stop the process.

### Outcome measurements

2.6

#### Primary outcome measurements

2.6.1

##### The change of meridian activities

2.6.1.1

The meridian activities and balance index will be measured and calculated with Ryodoraku device (Meridian Energy Analysis Device, MEAD, medpex, Taiwan). It will be measured 3 times: before intervention (baseline) and 1 and 2 hours after intervention. The meridian activities will be shown by numbers calculated by the skin electric resistance. The higher the number, the higher is the meridian activity, and vice versa. Before the Ryodoraku measurement, the participants need to take off their shoes and socks, remove all metal accessories, cellphone, medication, electronic devices on their body, clean their hands and feet, and lie down on the plastic bed. During the measurement, the participant must not contact any metal obstacle and the investigator will not touch the participant. The 12 measured Ryodotens will be as follows (Fig. 2): Taiyuan (LU9) on the Lung meridian, Daling (PC7) on the Pericardium meridian, Shenmen (HT7) on the Heart meridian, Yanggu (SI5) on the Small Intestine meridian, Yangchi (TE4) on the Tripple Energizer meridian, Yangxi (LI5) on the Large Intestine meridian, Taibai (SP3) on the Spleen meridian, Taichong (LR3) on the Liver meridian, Dazhong (KI4) on the Kidney meridian, Shugu (BL65) on the Bladder meridian, Qiuxu (GB40) on the Gallbladder meridian, and Chongyang (ST42) on the Stomach meridian. Each first detected data will be viewed as the activity of that Ryodoten.

